## Abstract

**Background:**

Surgery in patients with obstructive jaundice caused by a periampullary (pancreas, papilla, distal bile duct) tumor is associated with a higher risk of postoperative complications than in non-jaundiced patients. Preoperative biliary drainage was introduced in an attempt to improve the general condition and thus reduce postoperative morbidity and mortality. Early studies showed a reduction in morbidity. However, more recently the focus has shifted towards the negative effects of drainage, such as an increase of infectious complications. Whether biliary drainage should always be performed in jaundiced patients remains controversial. The randomized controlled multicenter DROP-trial (DRainage vs. Operation) was conceived to compare the outcome of a 'preoperative biliary drainage strategy' (standard strategy) with that of an 'early-surgery' strategy, with respect to the incidence of severe complications (primary-outcome measure), hospital stay, number of invasive diagnostic tests, costs, and quality of life.

**Methods/design:**

Patients with obstructive jaundice due to a periampullary tumor, eligible for exploration after staging with CT scan, and scheduled to undergo a "curative" resection, will be randomized to either "early surgical treatment" (within one week) or "preoperative biliary drainage" (for 4 weeks) and subsequent surgical treatment (standard treatment). Primary outcome measure is the percentage of severe complications up to 90 days after surgery. The sample size calculation is based on the equivalence design for the primary outcome measure. If equivalence is found, the comparison of the secondary outcomes will be essential in selecting the preferred strategy. Based on a 40% complication rate for early surgical treatment and 48% for preoperative drainage, equivalence is taken to be demonstrated if the percentage of severe complications with early surgical treatment is not more than 10% higher compared to standard treatment: preoperative biliary drainage. Accounting for a 10% dropout, 105 patients are needed in each arm resulting in a study population of 210 (alpha = 0.95, beta = 0.8).

**Discussion:**

The DROP-trial is a randomized controlled multicenter trial that will provide evidence whether or not preoperative biliary drainage is to be performed in patients with obstructive jaundice due to a periampullary tumor.

## Background

Patients with obstructive jaundice caused by a tumor in the pancreatic head area (pancreas, distal bile duct, papilla of Vater), without radiological evidence of irresectability, will undergo an exploration with the intention of resection of the tumor, being the only option for cure [1-4]. If a resection is not possible due to locoregional irresectability or distant metastases, a biliary and gastric bypass procedure is performed [5-8]. Surgery in jaundiced patients with a tumor in the pancreatic head area is associated with a higher risk of postoperative complications compared with surgery in non jaundiced patients [9-11]. These complications primarily consist of septic complications (cholangitis, abscesses, and leakage), haemorrhage, impaired wound healing and renal disorders. The increased risk of surgery in jaundiced patients was recognized already in 1935 by Allen O. Whipple, who proposed a two staged procedure for surgery in deeply jaundiced patients. The first stage consisted of a drainage procedure by a cholecystogastrostomy, to decompress the biliary tract in order to restore normal liver function, followed four weeks later by radical resection of the tumor [12]. Numerous experimental and clinical studies have been performed since, investigating the cause and directed at prevention of complications after surgery in patients with obstructive jaundice.

While the postoperative mortality rate after pancreatoduodenectomy has been reduced from around 20% to 1–5% in experienced centres, the morbidity rate has remained virtually unchanged, ranging from 40 to 60% [5,6,8,9]. Many different etiologic factors for development of complications have been characterized: presence of toxic substances as bilirubin and bile salts, impaired nutritional status, effects of endotoxins, bacterial translocation, modulation of the inflammatory cascade with cytokine release, reduction of cellular immunity and nutritional status [13-21]. For these etiologic factors different interventions have been undertaken in the past decades, attempting to lower the risk of complications. The current project addresses the issue of preoperative biliary drainage (PBD).

Early studies on external PBD could not demonstrate a reduction in complication rate in humans because this procedure, although relieving the biliary obstruction, does not restore the bile flow to the gut lumen [22]. Internal drainage has been shown in multiple experimental models to improve liver function and nutritional status, to reduce systemic endotoxemia and cytokine release, and subsequently to improve immune response [13-15,19-21]. Finally the mortality was significantly reduced in these animal models[16]. The first non-randomized studies on internal PBD in jaundiced patients reported a reduced mortality and morbidity [22]. However, clinical studies and small randomized trials could not confirm the positive effect of PBD on surgical outcome [23-27]. Some studies even reported a deleterious effect, partly due to complications associated with the drainage procedure [28-32]. Despite these results, PBD is generally accepted in The Netherlands. In previous studies we found that around 90% of patients with obstructive jaundice currently undergo preoperative drainage in The Netherlands [28,29]. The dominance of drainage can be attributed in part to the familiarity of endoscopic retrograde cholangiopancreatography (ERCP), which has been used in the past as the first diagnostic procedure for obstructive jaundice. The time needed for extensive diagnostic workup, including diagnostic laparoscopy (DL), is a logistic explanation for the assumed benefit of PBD. However, the value of DL for periampullary tumors is disputed, especially in the light of improvement of other non-invasive diagnostic procedures [1-4,33,34]. Other important factors that influence the decision to opt for PBD are (local) referral patterns and waiting lists. Current state-of-the-art radiological diagnostic and staging procedures for suspected periampullary tumors require only a minimum of time [1]. These non-invasive radiological procedures have the same diagnostic accuracy as ERCP, an invasive diagnostic procedure, and, moreover, offer the advantage of assessing local tumor extension as well as distant metastases [1-3]. Therefore, ERCP with subsequent drainage as part of a routine diagnostic workup is outdated.

ERCP and endoscopic sphincterotomy with insertion of biliary and pancreatic stents is a difficult gastrointestinal endoscopic procedure. Complications, such as haemorrhage, pancreatitis, perforation of the duodenal wall, cholangitis and stent occlusion cannot always be avoided and occur in approximately 10 percent of procedures [35,36]. Mortality as a consequence of the procedure is reported in 0.5%–1% of the cases [36]. The negative side-effects of PBD, such as an increase of infectious complications after surgery, has been the focus of attention in more recent studies [30-32]. It was concluded that the potential advantages of preoperative drainage fail to outweigh the negative effects [20,23,24,28-32].

In the light of the ongoing controversy of PBD, a meta-analysis of randomized clinical trials and comparative studies was carried out [37]. The aim of this study was to evaluate the efficacy of drainage in jaundiced patients compared with patients that underwent direct surgical treatment. No difference in mortality could be detected between both strategies, but overall complication rate in patients that underwent PBD was significantly higher compared with direct surgical treatment, 57.3% and 41.9% respectively (level I evidence). The mean overall hospital stay was increased by two weeks in patients that underwent biliary drainage. Unfortunately, most of the studies have methodological flaws (e.g. differences in drainage procedures, duration of drainage, internal vs. external drainage, surgical procedures, small sample size) and do not provide unequivocal treatment recommendations. Therefore, a prospective randomized trial addressing the effects of PBD is indicated. Especially, for the potential consequences of future treatment might be considerable; a shorter workup period, less invasive diagnostic procedures (ERCP) and a shorter time interval to surgery. The study focuses on complication rate (40–60%), the primary endpoint for most past studies.

## Methods/Design

### Study objectives

The proposed project involves a randomized multicenter trial to compare the outcome of "a preoperative biliary drainage strategy" (standard strategy) with that of an "early surgery" strategy, with respect to the incidence of severe complications (primary outcome measure), hospital stay, number of invasive diagnostic tests and costs.

### Study design

The DROP-trial is a randomized multicenter trial with four academic and ten regional hospitals participating in the project. Patients with obstructive jaundice (bilirubin level 40–250 μmol/l) due to a pancreatic/periampullary tumor, who are candidate for exploration after staging with CT scan, and scheduled to undergo a "curative" resection, will be randomized to either "early surgical treatment" (within one week) or "preoperative biliary drainage" (for four weeks) and subsequent surgical treatment (standard treatment) (figure 1). Randomization is centralized in the Academic Medical Center, Amsterdam, by means of a computer generated allocation with stratification for center.

**Figure 1 F1:**
[figure not shown]
DROP-study flowchart.

### Study population

The study population consists of patients with the clinical diagnosis of obstructive jaundice due to a pancreatic head or periampullary tumor. Inclusion criteria are; a serum bilirubin level of > 40 μmol/l and < 250 μmol/l at randomization, CT without evidence of distant metastases or local tumor ingrowth into portal or mesenteric vessels (as defined by the tumor surrounding the vessel for at least 180 degrees of the circumference), referred for surgical treatment to one of the participating centres, time between CT and randomization ≤ 4 days, informed consent. Exclusion criteria are; age > 85 years or severe co-morbidity (Karnofsky <50%) and other contraindications for major surgery, cholangitis/infection, previous ERCP and stenting or percutaneous biliary drainage, previous chemotherapy for this malignancy, severe gastric outlet obstruction (stenosis duodenum due to tumor ingrowth) defined as vomiting, nausea and/or oral intake less than one l/day.

### Primary outcome parameter

Primary outcome parameter are severe complications and the study is designed for detecting equivalence in the occurrence of these events during treatment within 120 days after randomization. This will include at least 90 days follow-up after surgery, a period selected as adequate, while > 95% of complications will occur within 30 days after surgery. A longer observation period up to one year will potentially include effects of progressive or recurrent disease.

A severe complication is defined as any complication, related to the drainage procedure and surgical treatment, leading to an additional invasive intervention or relaparotomy with subsequent prolonged hospital stay or death, or readmission for disease related morbidity within 120 days after randomization (table 1). The definition of all these complications, as well as their management, have been extensively evaluated in previous studies in our institution during the past 10 years according to generally accepted criteria [5,28,29,35,36,38,39].

**Table 1 T1:** Severe ERCP- and surgery-related (postoperative) complications [5,28,29,35,36,38,39,43,44].

	***COMPLICATION***	***CRITERIA***
***ERCP***		
	- Acute pancreatitis	Abdominal pain and a serum concentration of pancreatic enzymes (amylase or lipase) two or more times the upper limit of normal, that required more than one night of hospitalisation
	- Cholangitis	Elevation in the temperature to more than 38°C, thought to have a biliary cause, without concomitant evidence of acute cholecystitis
	- Acute cholecystitis	No suggestive clinical or radiographic signs of acute cholecystitis before the procedure and if emergency cholecystectomy is subsequently required
	- Perforation	Retroperitoneal or bowel-wall perforation documented by any radiographic technique
	- Haemorrhage	Clinical evidence of bleeding (melena or hematemesis) with an associated decrease of at least 2 g per decilitre in the haemoglobin concentration, or the need for a blood transfusion
	- Stent Occlusion	Recurring obstructive jaundice with necessary stent replacement
***SURGERY***		
	- Pancreatojejunostomy leakage	Drain output of any measurable volume of fluid on or after postoperative day 3 with an amylase content greater than 3 times the serum amylase activity, graded according to clinical course (ISGPS grade A, B, C)
	- Postpancreatectomy haemorrhage	Bleeding after the index operation requiring ≥ 4 units of packed cells and/or leading to relaparotomy/intervention
	- Delayed gastric emptying	Gastric stasis requiring nasogastric intubation for 10 days or more, or the inability to tolerate a regular (solid) diet on or before the fourteenth postoperative day
	- Biliary leakage	Bilirubin in abdominal drain or dehiscence found at laparotomy
	- Sepsis	Presence of two or more of the following: fever or hypothermia, leucocytosis or leucopenia, tachycardia, and tachypnea or a supernormal minute ventilation
	- Intra-abdominal abscess formation	Intra-abdominal fluid collection with positive cultures identified by ultrasonography or computed tomography, associated with persistent fever and elevations of white blood cells
	- Wound infection	Requiring intervention with subsequent prolonged hospital stay, otherwise considered as minor complication
	- Burst abdomen	
	- Any relaparotomy for other reasons	
	- Pneumonia	

To exclude bias in determining events of the primary endpoint, a blinded adjunction committee will review all events and evaluate whether events account as severe complications (with intervention, relaparotomy) needing prolonged hospital stay, or even a readmission.

### Secondary outcome parameters

Secondary endpoints are hospital stay, the number of (invasive) diagnostic procedures, medical and non medical costs, and quality of life. Quality of life will be measured for patients treated at the trial centre, at fixed intervals, by two validated questionnaires; the European Organisation for Research and Treatment of Cancer (EORTC) Quality of Life Questionnaire C-30 (QLQ-C30) and its Pancreatic Cancer Module (QLQ-PAN26) [40].

### Participating centres

Fourteen Dutch hospitals of the DROP-Trial group, including four academic centres and ten non-academic centres, are currently participating in this trial.

### Ethics

This study is conducted in accordance with the principles of the Declaration of Helsinki and 'good clinical practice' guidelines. The independent medical ethics committees of the participating hospitals have approved the study protocol. Prior to randomization, written informed consent will be obtained from all patients.

### Study outline

Patients may be included if CT scan has demonstrated a lesion in the pancreatic head area without metastases and/or local tumor ingrowth. Local physicians/gastroenterologists can refer patients for the study by contacting the primary trial centre or one of the participating centres (see addendum 1). Written informed consent will be obtained at the outpatient department according to the Guidelines of Clinical Research in Humans, when the patient meets the in- and exclusion criteria. Randomization is performed instantly by the trial centre.

After randomization, patients will be scheduled, either for surgical treatment within one week, or PBD with subsequent surgical treatment after four weeks. PBD is preferably performed by local gastroenterologists or in the referral centre according to local policy. The participating centres accepted to arrange extra operating room capacity to guarantee early surgery to be carried out when indicated.

#### ERCP + PBD

- ERCP with stent placement will be performed by an experienced endoscopist, by insertion of a single (plastic) stent

- If ERCP is not successful, the patient is to be referred to a tertiary centre for a second attempt for endoscopic drainage, or a percutaneous drainage will be performed, according to local preference and expertise.

- Biliary drainage is considered adequate if a decrease of > 50% of serum bilirubin level is found after two weeks of drainage; otherwise the stent should be changed.

- After four weeks of PBD, patients will undergo surgery. In case of complications indicating inadequate bile drainage and stent obstruction (cholangitis, stent occlusion) a stent exchange will be performed.

- Other complications, such as bleeding or severe pancreatitis, are treated according to the local generally accepted guidelines and could consequently lead to a delay of surgery [35,36].

- Preoperative nutritional support (e.g. consultation with a dietician) is recommended in patients with a weight loss of more than 15% during the last 3 months.

#### Surgery

- Surgery is planned keeping in mind the maximum estimated bilirubin level (> 40 μmol/l and < 250 μmol/l at randomization) must not exceed 300 μmol/l, 24 hours before surgery (e.g. high bilirubin at randomization requires earlier surgery).

- Vitamin K (10 mg, oral, 1 day preoperatively) is given on indication, cefuroxim (1500 mg, intravenous single shot, 1/2 hour preoperatively) and octreotide or analogues (3 × 100 μg, subcutaneous, 12 hours before surgery and continued for seven days after surgery) as prophylaxis.

- During exploration the standard procedure will be the standard pylorus preserving pancreatoduodenectomy (PPPD), as previously described, with removal of lymph nodes at the right side of the portal vein [33]. If indicated (suspicious ingrowth proximal duodenum/pylorus) a Whipple procedure is to be performed. In case of limited vascular ingrowth, a (wedge) resection of the portal/mesenteric vein might be performed [33,41].

- Reconstruction is performed by pancreaticojejunostomy, a hepaticojejunostomy and gastrojejunostomy [33].

- One silicone drain is placed near the pancreaticojejunostomy and/or one near the hepaticojejunostomy; T-drains will not be used.

- A feeding jejunostomy is not to be used as standard treatment

- If resection is not performed due to metastases or local ingrowth, biopsies have to be taken for a histological diagnosis.

Palliative treatment consist of a hepaticojejunostomy with gastroenterostomy plus a celiac plexus blockade [7,33,42]. If a hepaticojejunostomy is not possible, a Wallstent is inserted postoperatively by means of ERCP.

### Statistical analysis

#### Intention to treat

The analysis will be performed in accordance with the intention to treat principle.

#### Sample size calculation

The recently performed meta-analysis of randomized clinical trials and comparative studies, addressing the effectiveness of a PBD strategy in jaundiced patients versus a direct surgical treatment, did not show a difference in mortality between the two strategies [37]. The overall complication rates were, summarizing level I and II studies, 42% for the 'early surgery' strategy and 58.1% for strategy with preceding PBD.

The sample size calculation is based on the equivalence design for the primary endpoint, severe complications of treatment. Based on an expected 38% complication rate for early surgical treatment and 48% for preoperative drainage, equivalence is taken to be demonstrated if the percentage of severe complications with early surgical treatment is not more than 10% higher compared to standard treatment with PBD. Accounting for a 10% dropout, 105 patients are needed in each arm resulting in a study population of 210 (alpha = 0.95, beta = 0.8). If equivalence is found, the comparison of the secondary outcomes will be essential in selecting the preferred strategy.

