### Data analysis

The study is designed as an equivalence trial with respect to the primary outcome measure and superiority with respect to the secondary outcome measures. The principal analysis consists of an intention-to-treat comparison of the severe complication rate in both treatment strategies. The comparison will be expressed in terms of a relative risk and 95% confidence intervals. The research hypothesis will be evaluated using a two-group large-sample normal approximation test of proportions, with a one-sided 0.05 significance level. In addition, a comparison of the incidence of complications over time will be made using Kaplan-Meier estimates.

Subsequent analyses are directed at the secondary endpoints. The total number of additional procedures, the length of hospital stay, hospital-free survival and total costs will be compared using t-test statistics. Preplanned subgroup analyses include type of surgery (resection versus bypass), severity of jaundice and other risk factors for complications such as age > 70 years, weight loss > 10%, low albumin levels, renal function, low Hb (< 7 mmol/l), tumor pathology (papilla neoplasms, pancreatic head neoplasms and distal bile duct neoplasms).

An independent safety committee, consisting of three specialists (dept of internal medicine, dept of surgery, dept of clinical statistics), will guarantee the safety of the patients. After 105 included patients (50%), a blinded interim-analysis will be performed of all endpoints. Because of the delayed response for determination of the primary endpoint (severe complications), this analysis will be performed 120 days after randomization of the last patient to reach n: 105. The nominal significance (sequential two-sided testing) for the stopping rule is p < 0.01 (α = 0.01) for adverse effects (severe complications principal endpoint of safety analysis). Analysis will be performed for the individual groups and for the principal adverse effects.

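### The abstract (40%) and the sample-size section (38%) plan on different early-surgery rates for the same 105 per arm; 38% does not give 105 at the stated one-sided 0.05, and alpha and beta are mislabelled

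*Protocol article*

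**What the plan says.** The protocol article states the basis of the sample size twice.

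- Abstract, Methods/design: "Based on a 40% complication rate for early surgical treatment and 48% for preoperative drainage".
- Statistical analysis, Sample size calculation: "Based on an expected 38% complication rate for early surgical treatment and 48% for preoperative drainage".

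The other inputs agree in both places: 48% under drainage, a 10% margin in one direction, 10% dropout, and the same result, "105 patients are needed in each arm resulting in a study population of 210 (alpha = 0.95, beta = 0.8". The sample-size section words the margin as a requirement that "the percentage of severe complications with early surgical treatment is not more than 10% higher compared to standard treatment with PBD".

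The usable test level appears only in the Data analysis section, which specifies a "two-group large-sample normal approximation test of proportions, with a one-sided 0.05 significance level". The same paragraph adds: "The comparison will be expressed in terms of a relative risk and 95% confidence intervals".

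**The concern.** With all else equal, one sample size cannot follow from two different planning rates. The rate matters here because the expected advantage of early surgery adds to the margin: the distance to be detected is 18 points at 40% and 20 points at 38%. Nothing in the article explains the difference between the two figures.

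The error rates make it harder to see which calculation was done. A type I error of 0.95 and a type II error of 0.8 cannot be meant, so the sample-size text does not yield the design alpha. It has to be taken from the Data analysis section, where a one-sided 0.05 test stands beside a 95% interval, whose limits correspond to one-sided 0.025.

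The primary claim decides whether the secondary outcomes select the strategy, and it underlies the economic evaluation. Its stated basis should be open to checking.

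**Working it through.** **Inputs**
- Early-surgery rate pE: 0.40 (abstract) or 0.38 (Sample size calculation).
- Drainage rate pC: 0.48 (both places).
- Margin M: 0.10, read as absolute percentage points (an assumption, tested below).
- Test: normal approximation for two proportions, one-sided 0.05 (Data analysis), so z = 1.645.
- Power: 80%, which is how I read the printed beta of 0.8, so z = 0.842.
- Dropout: 10%.

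**Formula.** Evaluable patients per arm: n = (z_alpha + z_power)² × [pE(1 − pE) + pC(1 − pC)] / (M + pC − pE)². Randomised per arm: n / 0.9, rounded up.

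**Abstract's rate, one-sided 0.05** (reproduces the stated figure)
- Variance term: 0.2400 + 0.2496 = 0.4896. Distance: 0.10 + 0.08 = 0.18.
- n = 6.183 × 0.4896 / 0.0324 = 93.4, so 94. 94 / 0.9 = 104.4, so **105**.

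**Sample-size section's rate, one-sided 0.05**
- Variance term: 0.2356 + 0.2496 = 0.4852. Distance: 0.20.
- n = 6.183 × 0.4852 / 0.04 = 75.0, so 75. 75 / 0.9 = 83.3, so **84**, which is 21 per arm below 105.
- Variants at 38% and one-sided 0.05 also miss: dropout added as n × 1.1 gives 83, pooled variance 85, continuity correction 95, and 90% power 116. A plain superiority test needs 303 per arm before dropout.

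**Same rates, one-sided 0.025** (z = 1.960, squared sum 7.849)
- 38%: n = 7.849 × 0.4852 / 0.04 = 95.2. Then 95.2 × 1.1 = 104.7, so 105; 95.2 / 0.9 = 105.8, so 106; rounding first to 96, 96 / 0.9 = 106.7, so 107. The range is **105 to 107**.
- 40%: n = 7.849 × 0.4896 / 0.0324 = 118.6, so 119. 119 / 0.9 = 132.2, so **133**.

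**Check on the margin.** Read as 10% of 48%, the margin would be 4.8 points. At one-sided 0.05 the 40% rate would then need 6.183 × 0.4896 / 0.128² = 184.8 evaluable, and the 38% rate 6.183 × 0.4852 / 0.148² = 137.0. Neither leads to 105, which supports the absolute reading.

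**Power with 94 evaluable per arm** (105 × 0.9 = 94.5): Φ(distance / √(variance term / 94) − z_alpha).

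| Early-surgery rate | One-sided 0.05 | One-sided 0.025 |
|---|---|---|
| 40% | 80.2% | 70.3% |
| 38% | 87.3% | 79.5% |

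**The case against.** The strongest reply is that nothing operational is wrong. Confidence of 95% and power of 80% are evidently what the printed alpha and beta stand for, the test level is given elsewhere, and 210 patients are enough under either rate. This stands as a limit on the harm. It does not make the two rates compatible, and it does not make the sample-size section reproduce its own number.

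A second reply is that 38% may be right. It is the figure in the section that governs the sample size. At one-sided 0.025, with dropout added as n × 1.1, it gives 105, and that level fits both the printed 0.95 read as a confidence level and the planned 95% interval. This also stands, and it rules out the tempting inference that 38% is simply a misprint for 40%. Against it is the Data analysis section, which tests "with a one-sided 0.05 significance level". Two input sets lead to 105, and the document does not decide between them.

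A reader might also set 87.3% against 70.3% and speak of a 17-point uncertainty in power. That comparison joins the abstract's rate to an alpha that the stated test does not use. Under the stated test the spread is 87.3 − 80.2 = 7.1 points.

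**Conclusion.** The point holds as an error in the stated basis of the sample size. The two rates conflict, 38% gives 84 rather than 105 per arm under the one-sided 0.05 test, and the alpha and beta figures are wrong as labelled in both places. Of the sets consistent with the Data analysis section as written, 40% against 48% is the one that reproduces 105. This favours it but does not prove it, since 38% at one-sided 0.025 gives 105 to 107.

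A reader might infer that the trial is the wrong size or underpowered. The document does not support that: with 94 evaluable per arm and the stated test, power is at least 80% at either planning rate. Nor does the mislabelling mean that the trial runs with a 95% type I error and 20% power, because the Data analysis section fixes the test level.

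The conclusion assumes an absolute margin, an unpooled normal approximation, and 80% power as the meaning of the printed beta.

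**What to change.** Confirm from the sponsor's own sample-size calculation which early-surgery rate and which alpha were used. Then state one set in the abstract, the Sample size calculation section and the Data analysis section:

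- **(a)** 40% against 48%, margin 10 percentage points, one-sided alpha 0.05, power 80% (beta 0.20), 94 evaluable and 105 randomised per arm, with power of 87% noted if the early-surgery rate is 38%. This set agrees with the Data analysis section as it stands.
- **(b)** 38% against 48%, the same margin, one-sided alpha 0.025, power about 80%, with the test level in Data analysis changed to 0.025 to match, and power of about 70% noted if the rate is 40%.

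In either case, replace the printed alpha and beta in both places, say that the margin is in absolute percentage points, and check that the planned confidence interval corresponds to the alpha chosen.

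The cost is a correction of stated figures and, under (b), a change to the stated test level. The target stays at 210.
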